## Abstract

Introduction: Patients with neurogenic lower urinary tract dysfunction (NLUTD) reliant on intermittent self-catheterization for bladder emptying are at an increased risk of recurrent urinary tract infections (rUTI). So far, the most common practice in the prevention of rUTIs is long-term low-dose antibiotic prophylaxis, phytotherapy, and immunomodulation, whereby antibiotic prophylaxis inevitably leads to the emergence of drug-resistant pathogens and difficulty in treating infections. Therefore, non-antibiotic alternatives in the prevention of rUTIs are urgently required. We aim to identify the comparative clinical effectiveness of a non-antibiotic prophylaxis regimen in the prevention of recurrent urinary tract infections in patients with neurogenic bladder dysfunction who practice intermittent self-catheterization. Methods and analysis: In this multi-centre, prospective longitudinal multi-arm observational study, a total of 785 patients practising intermittent self-catheterisation due to NLUTD will be included. After inclusion, non-antibiotic prophylaxis regimens will be instilled with either UroVaxom^®^ (OM-89) standard regimen, StroVac^®^ (bacterial lysate vaccine) standard regimen, Angocin^®^, D-mannose (oral dose 2 g), bladder irrigation with saline (once per day). The management protocols will be pre-defined, but the selection of the protocol will be at the clinicians’ discretion. Patients will be followed for 12 months from the onset of the prophylaxis protocol. The primary outcome is to identify the incidence of breakthrough infections. The secondary outcomes are adverse events associated with the prophylaxis regimens and the severity of breakthrough infections. Other outcomes include the exploration of change in susceptibility pattern via the optional rectal and perineal swab, as well as health-related quality of life over time (HRQoL), which will be measured in a random subgroup of 30 patients. Ethics and dissemination: Ethical approval for this study has been granted by the ethical review board of the University Medical Centre Rostock (A 2021-0238 from 28 October 2021). The results will be published in a peer-reviewed journal and presented at relevant meetings. Study registration number: German Clinical Trials Register: Number DRKS00029142.

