We have recourse to a broad armamentarium of non-antibiotic options, whereby significant evidence is limited. Several viable and readily available options have been shown to yield consistent results. Main alternatives to antibiotic prophylaxis include vaccines, antiseptics, urine-specific antimicrobials, and direct mechanic washouts of the bladder. A variety of vaccines have been used in the prevention of rUTIs. Especially OM-89 (Urovaxom^®^) and the bacterial lysate vaccine Strovac^®^ have been diligently tested and proven to lower the rate of UTI [3,4,5,6]. Additionally, a wide variety of phytotherapeutics is currently in use, especially in Eastern medicine, as a cost-effective and low-threshold, whereas ambivalent efficacy has been reported. A combination of Tropaeoli majoris herba (Nasturtium) and Armoraciae rusticanae radix (Horseradish) demonstrated excellent safety and efficacy in the prevention of recurrent UTIs [7,8]. D-Mannose is another beneficial and cheap prophylactic, therapeutic agent in rUTI with very few side effects [9,10]. Bladder irrigation with various agents, e.g., neomycin, acetic acid, or sterile saline, is also widely used in order to lower bacterial load and defer sedimentation [11,12,13]. 

The main aim of our study is to identify the comparative clinical effectiveness of non-antibiotic prophylaxis regimens in the prevention of rUTI infections in patients with neurogenic bladder dysfunction who practise clean intermittent self-catheterization (CISC). The primary outcome is depicted by the number of breakthrough infections. Secondarily adverse events associated with the prophylaxis regimens and the severity of breakthrough infections must be investigated. 

Change in susceptibility pattern via the optional rectal and perineal swab, as well as health-related quality of life over time (HRQoL) outcomes, will be measured in a random subgroup of 60 patients.

The primary objective is to identify the clinical effectiveness of different prophylactic regimens. The secondary objective is to determine the adverse events related to prophylaxis and the severity of breakthrough infections. 

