## 3. Design

This is a prospective, longitudinal, multi-arm, multi-centre, observational, clinical cohort study. Patients will receive approved non-antibiotic UTI prophylaxis with either *Escherichia coli* viva OM-89 (UroVaxom^®^), bacterial lysate vaccine (StroVac^®^), nasturtium and horseradish root powder (Angocin^®^), D-Mannose or bladder irrigation with saline once daily. Occurring complications under named prophylaxis will be treated according to the current standard of care. 

Primary Outcome Measure: Incidence of symptomatic breakthrough infections.

Secondary Outcomes: Severity of infectious breakouts with antibiotic use, development of antibiotic-resistant (AMR) flora, number of antibiotics used, quality of life, and exploration of health economic assessment variables. 

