### 4.2. Exclusion Criteria

Patients practising ISC with augmented bladder or continent pouches;Inability to consent;Intention-to-treat analysis for dropouts;Failure to provide consent;MDR pathogens in previous episodes of UTIs;Antibiotic prophylaxis in the months before study enrolment.

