### 6.2. Non-Antibiotic Prophylaxis Regimen

UroVaxom (OM-89) will be administered as a standard regimen: once daily for three months with a three-month pause following and three ten-day cycles at 7, 8 and 9 months.,StroVac (bacterial lysate vaccine) standard regimen: three vaccines in 6–12 weeks with two weeks between each vaccination *.Angocin twice daily for the duration of the study.D-mannose (oral dose 2 g) once daily for the duration of the studyBladder irrigation with saline (0.9%; 250 mL) once per day for the duration of the study.

* In case of restricted drug availability due to country-specific authorisation of vaccines, additional treatment arms with similar mechanisms of action will be opened and analysed as a subgroup. If necessary, amendments to the protocol will be issued, and additional ethics approval will be requested.

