## 7. Statistical Considerations

Power analysis was performed to determine an adequate sample size. We considered that these patients suffer 9.4 UTIs per year with an SD of 5.414. Furthermore, we assumed that a reduction of 3 UTIs per year is clinically significant. In order to achieve an effect size of 0.1, 785 participants are necessary (power = 0.87; alpha = 0.05). Furthermore, to achieve an effect size of 0.2, 197 participants are necessary, or for an effect size of 0.3, 88 participants are required, respectively. Data measured on a continuous scale will be expressed as mean, standard deviation, range, and median. Counts and percentages of patients in the categories will be used to convey categorical data. When necessary, T- or Mann-Whitney tests will be performed to determine statistical differences in continuous variables, and Chi-square or Fisher’s tests will be used to test for statistical differences in categorical variables.

Patients with a minimum follow-up of 6 months who remained on the same prophylaxis regimen will be eligible for the final statistical analysis. 

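### Section 7 restricts the final analysis of every outcome to patients who stayed 6 months on one regimen, which selects on persistence and sits in tension with the intention-to-treat line in Section 4.2

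*Protocol article*

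**What the plan says.** Section 7 (Statistical Considerations) has one sentence on who is analysed: "Patients with a minimum follow-up of 6 months who remained on the same prophylaxis regimen will be eligible for the final statistical analysis". It covers the final analysis as a whole and names no outcome that escapes it.

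Section 4.2 lists, among the exclusion criteria, "Intention-to-treat analysis for dropouts". This is the only other statement on how dropouts are analysed.

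The outcomes affected are these:
- Section 3: "Primary Outcome Measure: Incidence of symptomatic breakthrough infections".
- Abstract: "The secondary outcomes are adverse events associated with the prophylaxis regimens and the severity of breakthrough infections". Section 1.1 agrees: "The secondary objective is to determine the adverse events related to prophylaxis and the severity of breakthrough infections". The lists in Sections 2.2 and 3 do not include adverse events.

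Planned follow-up runs past the 6-month mark: "Patients will be followed for 12 months from the onset of the prophylaxis protocol". Section 6.2 gives Angocin, D-mannose and saline irrigation throughout the study. UroVaxom is given "once daily for three months with a three-month pause following and three ten-day cycles at 7, 8 and 9 months", and StroVac as "three vaccines in 6–12 weeks with two weeks between each vaccination".

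Section 6.4 records the reason for and timing of dropout, UTI, adverse events, administration problems, time on the regimen and any switch. Section 7.3 says that adverse events will be investigated and reported.

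**The concern.** Being analysed depends on what happens after the regimen starts. A patient who has breakthrough infections and moves to another regimen at month 4 is a failure of the first regimen, yet the rule takes that patient out. The same holds for a patient who switches or leaves early because the regimen is not tolerated. Both kinds of event are on the Section 6.4 list, so the plan foresees them and records them, and then sets them aside.

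Section 2 says the study is meant to find safe and effective candidates for a randomised trial. Early failure and early intolerance are the information that choice needs most. The regimen is chosen by the clinician, so the comparison is already open to confounding; selection on persistence adds a second distortion. The one line that would bring dropouts back in stands in the exclusion criteria, where it cannot work as an eligibility criterion.

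**Working it through.** **1. The two statements, patient by patient**

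| Patient | Section 7 | Section 4.2 line, if read as an analysis rule |
|---|---|---|
| Leaves follow-up before month 6 | removed | kept |
| Switches before month 6, still followed | removed | kept if a switch counts as dropout (Section 6.4 records switches there) |
| Leaves or switches after month 6 | kept if staying on regimen is judged over the first 6 months or up to leaving; removed if over 12 months | kept, with the same proviso for a switch |
| Stops StroVac or UroVaxom early, no switch, followed to month 6 | unclear | unclear |

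The statements can agree after month 6. They pull apart before it.

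The last row is unclear because of the schedules. A StroVac course is over in 6 to 12 weeks (about 1.4 to 2.8 months). UroVaxom has a planned pause in months 4 to 6 and a total intake of about 3 months + 3 × 10 days = 4 months. At month 6, neither patient would be taking anything under the plan.

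**2. What the rule can do to an adverse-event share**

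The plan gives no figure to reproduce here, and no adverse-event, stopping or switching rates. All rates below are assumptions; 785 is the planned sample size, used only for scale.

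Let p be the share of starters with an adverse event, f the fraction of these removed by the rule, and g the fraction of the other starters removed.

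Reported share = p(1 − f) / [p(1 − f) + (1 − p)(1 − g)]

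| | g = 0 | g = 10% | g = 20% | g = 30% |
|---|---|---|---|---|
| p = 15%, f = 20% | 12.4% | 13.6% | 15.0% | 16.8% |
| p = 5%, f = 20% | 4.0% | 4.5% | 5.0% | 5.7% |

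First cell: the numerator is 0.12 and the denominator is the sum of 0.12 and 0.85, which gives 12.4%. At p = 15%, 785 × 0.15 = 117.75 starters have an adverse event and 117.75 × 0.20 = 23.55, about 24, are removed. The share is too low if f > g, unchanged if f = g, and too high if f < g.

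**3. Between regimens**

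Take p = 15% in two regimens, with removal in the second at half the fractions of the first.
- f = 20%, g = 30% against f = 10%, g = 15%: 16.8% against 15.7% (numerator 13.5%, denominator the sum of 13.5% and 72.25%). The regimen with more removal looks worse.
- f = 20%, g = 10% against f = 10%, g = 5%: 13.6% against 14.3% (numerator 13.5%, denominator the sum of 13.5% and 80.75%). The regimen with more removal looks better.

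So no direction can be claimed.

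**4. Primary outcome**

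Let d be the share of starters removed and D their excess in UTIs per year over those kept. The mean in all starters is (1 − d)K + d(K + D) = K + dD, where K is the mean in those kept, so the reported mean is too low by dD. With D = 3 and d = 10, 20 or 30%, this is 0.3, 0.6 or 0.9 UTIs per year. With D = 0 it is zero. The value 3 is borrowed from the reduction that Section 7 calls clinically significant; nothing in the documents says that removed patients differ by that much.

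**The case against.** **The Section 4.2 line is only a fragment.** It names no outcome and no analysis set, and it may be an editing slip or may mean a separate analysis of dropouts. This stands. A reader might infer that the protocol lays down two clear rival rules, and that adverse events of early stoppers are certainly analysed under Section 4.2. The text shows less: an ambiguous, misplaced line in tension with Section 7.

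**Adverse events are not in the formal lists.** Sections 2.2 and 3 omit them, so Section 7 may not have been written with them in mind. This also stands, and it makes adverse events one consequence beside the primary outcome. It does not remove the point, since the abstract and Section 1.1 name them and Section 7 exempts nothing.

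**Analysis sets belong in the analysis plan, and Section 7.3 covers reporting.** The lack of a separate safety set is indeed no finding in an article. The finding is the rule that the article does state. A reader might go further and infer that adverse events will go unreported. Section 7.3 speaks against that, but it describes the handling of events under audit and does not change who enters the comparison of regimens.

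**The removal is not complete.** A reader might infer that every adverse event leading to a stop before month 6 is lost. The documents support this only for patients who switch or leave follow-up before month 6. For StroVac and UroVaxom patients who stop without switching, the text does not decide.

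**Conclusion.** The concern holds as a badly fixed rule. Section 7 makes inclusion in the final analysis conditional on 6 months of follow-up on one regimen, for all outcomes, and is in tension with Section 4.2. Patients who switch or leave follow-up before month 6 are removed, including those who do so because of a UTI or an adverse event. This follows from the wording alone and needs no assumed rate.

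The size does need assumed rates, and the documents supply none. The illustrations show what is possible: a 15% adverse-event share reported as 12.4% to 16.8%, and a mean UTI rate too low by 0 to 0.9 per year. A reader might infer that the rule always flatters tolerability, or favours a particular regimen. Neither is supported: the share is too low only where patients with an adverse event are removed more often than the others, and the direction between regimens can go either way.

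This should be corrected before the analysis, since the set affects both the primary outcome and tolerability.

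**What to change.** In Section 7:

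1. Limit the present sentence to a named analysis: *The on-regimen effectiveness analysis includes patients with at least 6 months of follow-up on the same regimen.* State whether staying on regimen is judged over the first 6 months or the full 12, and define it for StroVac (for example, by injections received) and UroVaxom (for example, by the daily phase, allowing for the planned pause).
2. Move the intention-to-treat line from Section 4.2 and word it: *Breakthrough UTIs are also analysed in all patients who started a regimen, by the regimen started, as a rate per person-time over all available follow-up.*
3. Add: *Adverse events, and stops or switches due to them, are reported for all patients who started a regimen, by the regimen started, with time on regimen shown.* Time on regimen matters because planned intake runs from 6 to 12 weeks (StroVac) through about 4 months (UroVaxom) to 12 months (the other three).

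The cost is a few sentences, one moved line and one or two extra tables. Section 6.4 already records the reason and time of dropout, time on regimen and any switch, so no extra patients or visits are needed. Unequal follow-up calls for a rate analysis in addition to the t and Mann-Whitney tests named in Section 7.

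The downsides are two effectiveness results to report and adverse-event rates that may be higher. Where follow-up ends at dropout or switch, the all-starters result rests on the follow-up collected and is not full intention-to-treat; the report should say so.

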### 7.1. Patient and Public Involvement

Patients or the public were not involved in the design, conduct, reporting, or dissemination plans of our research.

### 7.2. Protocol Amendments

If protocol amendments are necessary, all involved parties (e.g., participating and recruiting institutions, local investigators, data analysts etc.) will be notified before relevant changes come into place.

### 7.3. Trial Audit

The trial will be audited by primary investigators after each data collection point. If any adverse events occur in between, those will be investigated, addressed, and reported accordingly.

## 8. Management

The Global Prevalence Study on Infection (GPIU) study team and platform will provide adequate data management.

## 9. Administration, Logistics & Quality Assurance

### 9.1. Sharing of Observations

The collection of observational data will be performed using electronic (e) case report forms (CRF). Sites will receive direction from the study coordinator to help them complete the eCRFs. The research team retains the right to modify or enhance the eCRF template as necessary. Sites should utilise revised or extra forms, as these changes do not constitute a protocol amendment.

### 9.2. Central Data Monitoring

The study coordinator will examine the completed eCRFs for consistency with the protocol, protocol compliance and missing variables. If any data gaps or anomalies are discovered, the site will raise questions for resolution. It is possible to query any systemic discrepancies found through central data monitoring.

### 9.3. Definition of End of Study

The end of the study will be the date of the last observation captured of our last enrolled participant.

## 10. Research Governance

### 10.1. Sponsor Responsibilities

To date, no sponsors have been named.

### 10.2. Participating Sites Responsibilities

Responsibilities delegated to participating sites are defined in an agreement between the Sponsor and the individual site.

## 11. Participant Protection and Ethical Considerations

### 11.1. Approvals

The cohort study is designed longitudinal, observational with no intervention with no patient identifiable data and, generally, should not need ethics review. As this might differ between countries, the investigating sites should retrieve ethical consent according to their local needs. Ethical approval was granted in Germany by the ethical review board of the University Medical Centre Rostock (A 2021-0238 from 28 October 2021). In case of a change of protocol, amendments from country-specific ethical committees will be requested. 

### 11.2. Conduct

This registry will be conducted according to the approved protocol and its amendments, supplementary guidance, and manuals supplied by potential sponsors.

### 11.3. Data Protection Act (DPA)

Data collected during the course of the study will be kept strictly confidential and accessed only by members of the team. Participants’ details will be stored on a secure database under the guidelines of the 1998 Data Protection Act, and regular checks and monitoring are in place to ensure compliance. Data are stored securely in accordance with the Act and archived in a secure data storage facility. The IT manager at Rostock University, Germany (in collaboration with the Study Directors and study coordinator) will manage access rights to the data set. Participants will be allocated an individual-specific number, and their details will be anonymised on the secure database. We anticipate that anonymised data may be shared with other researchers to enable international prospective meta-analyses. To comply with the 5th Principle of the Data Protection Act 1998, personal data will not be kept for longer than is required for the purpose it has been acquired.

## 12. Publication Policy

The main results will be published in peer-reviewed journals on behalf of all collaborators. The manuscript will be prepared by a writing group of members of the scientific committee and the European Section of Infections in Urology. Group authorship will be inserted under the collective title of ‘the NAPRUN Study Management Group’. If one or more individuals have made a significant contribution above and beyond other group members, but where all group members fulfil authorship rules, authorship will be attributed to the named individual(s) and the NAPRUN Group. Participating clinicians may be selected to join the writing group based on intellectual and time input. All participating clinicians will be acknowledged in the publications. Any presentations and publications relating to the data must be authorised by the GPIU group.

## Data Availability

Data will be available on request due to restrictions e.g., privacy or ethical. The acquired data in this study will be available on request from the corresponding author. The data won’t be publicly available due to the General Data Protection Regulation by the European Union.
